## Abstract

Promoting a healthy sleep is a big challenge and becomes a strategic priority in public health, due to the severe consequences on children’s development and risk to psychiatric diseases. Interventions that promote healthy sleep, such as those that focus on the dissemination of behavioral and environmental recommendations of sleep hygiene with children, are presented as an alternative. Serious game design offers wide-reaching domains in health applications and is increasing in popularity, particularly with children and teens because of it’s potential to engage and motivate players differently from other interventions. This study aims to evaluate effects of serious game on sleep hygiene recommendations “Perfect Bedroom: learn to sleep well,” on sleep habits and sleep parameters of healthy children. This is an experimental, prospective and quantitative study. We will randomize children in experimental (*n* = 88) and no intervention groups (*n* = 88). The experiment has four stages (pre-intervention, intervention, post-intervention, and follow-up), which will count with participation of children and their parents/guardians. In the evaluation stages, the guardians will answer questionnaires and scales to assess sociodemographic and health data, sleep habits and sleep pattern of their child. The children themselves will answer the following: a scale to assess sleepiness levels, a questionnaire to evaluate the serious game and the game itself, will characterize their bedroom and the activities they perform before sleep, with strategies developed by researches. Intervention with experimental group conducted with the serious game “Perfect Bedroom” will happen twice a week, for 3 weeks in a row, resulting in six sessions of 50 min each. Inferential analysis will be conducted for comparisons between groups and intragroups to measure effect of intervention in primary outcomes (sleep habits) and secondary outcomes (sleep parameters). We expect that the intervention with this game can provide valuable evidence to a new approach in promoting healthy sleep habits, with applications in clinical, educational, and familiar settings, which could diminish future health issues and risk at psychiatric diseases, decreasing the social burden of treatments for these conditions in children.

## Introduction

Sleep in children is a critical component for development and health, becoming an important call for action over the 21st century (Gruber et al., 2016). Sleep health is a “multidimensional pattern of sleep-wakefulness that promote physical and mental well-being,” and it includes seven potential domains that are considered in literature as predictors of health outcomes: Duration (total of sleep obtained in 24 h), Continuity (ability of falling asleep and returning to sleep when waking up without necessity), Timing (the time of sleep within the 24-h), Sleepiness/Alertness (ability to maintain attentive wakefulness); Quality (subjective evaluation of “good” or “poor” sleep); Regularity (consistency of sleep and wake times) and Rhythmicity (overall circadian rhythm pattern) (Buysse, 2014; Wallace et al., 2018).

This concept could be applied for children based on prior scientific evidences of negative consequences of children not getting enough sleep and/or poor sleep quality, such as irregularity in sleep schedules (Mindell et al., 2009; Matricciani et al., 2012; Kelly et al., 2013; Buysse, 2014; Paruthi et al., 2016). Literature data indicates association between deficits in these domains and negative outcomes, demonstrating critical role of sleep to physical, cognitive and psychological developmental process (Biggs et al., 2011; Boe et al., 2012; Simola et al., 2012; Turnbull et al., 2013; Brand et al., 2016; Gregory and Sadeh, 2016; Williams et al., 2016). A number of studies highlight evidences of consequences inappropriate sleep during development in presence of lower school performance, emotional and behavioral problems, decreased cognitive function (e.g., memory, attention, executive functions), health problems (e.g., increased risk of obesity, hypertension, diabetes), poor mental health and risk of psychiatric diseases in adolescence or adulthood (e.g., anxiety disorder, depression symptoms, oppositional defiant disorder, borderline personality disorder symptoms), lower quality of life and wellbeing (Kirov and Brand, 2011; Astill et al., 2012; Boe et al., 2012; Araújo and Almondes, 2013; Kelly et al., 2013; Shanahan et al., 2014; Csábi et al., 2015; Nelson et al., 2015; Chaput, 2016; Paruthi et al., 2016; Reidy et al., 2016; Lereya et al., 2017; Quach et al., 2018)

Additionally, secondary effects of such condition can be identified in the child’s family, as the following: negative impact on sleep quality, daytime functioning and subjective well-being; and the presence of depressive symptomatology, fatigue, stress, and conjugal conflicts (Meltzer and Mindell, 2007; Sadeh et al., 2010; Kelly and El-Sheikh, 2011). Similarly, children and teenagers’ sleep patterns is associated with parental sleep patterns and family functionality (Kalak et al., 2012; Bajoghli et al., 2013; Urfer-Maurer et al., 2017), especially on infants (Brand et al., 2009). This bi-directional association could be explained by: (1) influence of socioeconomic status (SES) in functionality and environment, (2) parenting style and psychological function of parents, and (3) correspondence of inadequate sleep habits between parents and their child (Bajoghli et al., 2013; Urfer-Maurer et al., 2017).

Insufficient and irregular sleep could be influenced in part by poor sleep hygiene (Mindell et al., 2015; Brockmann et al., 2016; Brambilla et al., 2017). Study with caregivers reports indicate that sleep hygiene is associated with how well children ages 0–10 years sleep (Mindell et al., 2009). Sleep hygiene practices includes a set of behavioral and environmental recommendations on sleep environment, sleep routine and daytime activities with the aim of promoting healthy sleep (Irish et al., 2015).

Common sleep hygiene practices in the sleep environment include providing a comfortable bedroom, without excessive noise or distracting stimuli, and with adequate temperature and luminosity. Promotion of a sleep routine is significantly important for children, as it helps to maintain consistent sleep schedules on school days and weekends, and to avoid sleep deprivation. Additionally, a bedtime routine could be composed by activities that help prepare the child to fall asleep, such as: reading, talking about the day, bath time and story-telling (Irish et al., 2015; Allen et al., 2016).

The National Sleep Foundation’s recommendations on sleep duration indicate that school-age children, focus of this study, should sleep in between 9 and 11 h. Still, in this age it is observable widespread use of technology, with increased use of mobile devices (Hirshkowitz et al., 2015; Brockmann et al., 2016). There is as well an increasing demand of their time on school, extracurricular and social activities (Kelly and El-Sheikh, 2011).

Several studies discuss that exciting activities and use of video devices near bedtime (e.g., television, tablet, video game, smartphones), an uncomfortable sleeping environment, and/or irregularity of bedtimes and waketimes are related to sleep onset-delay, shorter sleep duration, later bedtime and increased daytime sleepiness (Mindell et al., 2009; Cain and Gradisar, 2010; Hale and Guan, 2015; Allen et al., 2016; Brambilla et al., 2017).

While literature reports these negative effects of poor sleep hygiene, there is still difficulty to translate research in pediatric sleep into effective actions and policies that may change this condition. Recent manuscripts identify just 15 studies aiming to improve sleep of children and teenagers (Gruber et al., 2016; Blunden, 2017). Sleep interventions have been applied in family, school and clinical contexts, involving parents, teachers, and children, resulting in improvements in knowledge about sleep and promoting few changes in sleep behaviors (Wilson et al., 2014; Blunden and Rigney, 2015; Ashton, 2017; Blunden, 2017).

The intervention “Sweet Dreamzzz Early Childhood Sleep Education Program^TM^” was conducted with teachers, parents, and pre-school children. During eight school days children received lessons about the following topics: bedtime routine and importance of sleep before 08:00 pm. The researchers used recreational resources, such as: one bear named Teddy, stories about sleep and one BINGO. This intervention improved the parent’s knowledge about sleep, attitudes and self-efficacy immediately post-intervention, without lasting effects. As secondary outcomes, visible improvement was only in sleep duration, with a 30 min increase; however, said increase was evaluated through subjective measures in sleep diaries answered by parents, and the children’s knowledge has not been assessed (Wilson et al., 2014).

Other study, also involving teachers, parents and children improved in 10 min sleep duration of children with ages between 11 and 13 years but did not identify changes in sleep knowledge and sleep habits. In this study, lessons were delivered with Microsoft Power Point Presentations about sleep physiology and hygiene. Similar to the study of Wilson et al. (2014) the assessment of sleep behavior was not objectively measured and the classroom attendance was not evaluated, which could indicate different levels of exposition of sleep education program (Rigney et al., 2015). Along with intervention on children’s health, there are sleep training interventions in clinical contexts that aim to improve emotional, behavioral, and/or social performance through healthy sleep. Keshavarzi et al. (2014), developed a 12-week sleep training intervention for children with attention deficit/hyperactivity disorder (ADHD), which included recommendations on sleep hygiene and orientations to define both sleep and wake-up times, to gradually improve sleep duration. Results from this research showed improvements on sleep, mood, and relationships with familiar and friends.

There are also interventions that include just parents. Mindell et al. (2016) examined efficacy of a sleep hygiene educational campaign “Sleep Well” directed to parents and developed with families of low SES assisted by One House at a Time’s Beds for Kids, which provides beds for children of these families. Thus, the study had two groups: the sleep education group received the following three sleep messages in three objects (sheet, on a bookmark, and on a refrigerator magnet): (1) have a bedtime before 09:00 pm, (2) avoid caffeine, and (3) keep electronics out of the bedroom. The control condition group received a packet with information about dental education. Results from this research indicate that alterations in sleep environment were associated with the increase in sleep duration and reduction in electronics devices present in the bedroom for all children, but the intervention group showed more benefits in the decrease of electronics devices in bedroom and extension of nocturnal sleep (Mindell et al., 2016). The relationship between sleep and lower SES has been explored, with children from lower income and/or maternal education families experiencing sleep problems, such as difficulties in initiating and/or maintaining sleep; and a shorter time in bed (Boe et al., 2012).

Another intervention with parents in a pediatric primary care clinic verified that a simple, punctual and inexpensive educational tool, such as one brochure, may improve parent’s knowledge about healthy sleep in childhood, as well as increase the number of caregivers that planned to change inadequate sleep habits for children (Jones et al., 2013). However, this research also did not provide an objective measure of children’s sleep, since self-report intentions to improve sleep could be based on social desirability by the parents.

These studies present intervention proposals with limitations. First, sleep patterns assessment in most cases is by subjective measures and answered by parents. Recent reviews indicated that the caregiver’s knowledge about sleep needs and routine is poor (McDowall et al., 2017); the parental perception of sleep amounts is complex and limited to parental perception of children’s sleep behaviors, which could influence in sleep diaries accuracy (Jones et al., 2013; Sadeh, 2015).

Ecological assessment of the children’s knowledge about interventions themes in baseline and post-intervention was not included in any of the researches, but one study used a Sleep Knowledge Questionnaire to assess this parameter (Rigney et al., 2015). Furthermore, just one study used non-randomized trials to allocate school and children in intervention or control conditions.

Therefore, there is a big gap in the interventions described, which is the inclusion of a motivational approach to increase interest and involvement of participants, especially the children themselves, as several interventions only receive information from parents. In view of this gap and the increase in use of serious games on: (1) health, with the purpose of promoting quality of life and healthy habits; (2) cultural training; (3) professional learning and training; (4) social skill training; (5) to support and help decision making and (6) to teach, motivate and help in formal education (Blumberg and Burke, 2014; Calderón and Ruiz, 2015; Boyle et al., 2016; Mahlmann et al., 2017), our research team proposes that it may be used as an integrable tool to Sleep Hygiene, in order to include the fantasy and playful components in this type of intervention for children.

The main objective of this type of game is to promote formal and informal health education, in addition to behavioral modification (Blumberg and Burke, 2014). It can be classified according to the application platform, as digital and non-digital. The first category involves human interaction with user interfaces from any electronic devices (cell phone, tablet, computer), which promote user feedback, while non-digital users interacts with other resources, such as boards, cards, papers, and pencils (Mitamura et al., 2012; Petri and von Wangenheim, 2016).

Previous research indicated the potential of serious games for the promotion of a healthy lifestyle, suggesting that serious gaming interventions alone or with an educational module have a positive effect in these parameters (DeSmet et al., 2014; Lau et al., 2017). There are games that aim to promote healthy eating, regular physical activity, safe sexual behavior and the management of chronic illnesses (Scarle et al., 2011; DeSmet et al., 2015; Viggiano et al., 2015). On the same vein, interventions with exergames (active videogames) have been used also to improve behavior, physical skills and in rehabilitation (Navarro et al., 2017). This could promote benefits in others parameters, such as sleep (Mahlmann et al., 2017). However, even with the wide dispersion of intervention using games, there are still few studies that validate the effectiveness of this type of intervention (Moreno-Ger et al., 2014).

For children, serious games are an ideal approach and can become a promising intervention modality, since playing games is a popular leisure for the new generations. The idea is that a serious game could enhance engagement by features of game design, types of interaction and user’s experience (entertainment), which provide positive experiences that maintain the player’s involvement and increase exposure of health intervention (Baranowski et al., 2016).

In this way, our research team developed a serious game based on recommendations of Sleep Hygiene, named “Perfect Bedroom: learn to sleep well.” Considering the potential benefits of these approaches taken together, we hypothesized that an intervention with the serious game “Perfect Bedroom: learn to sleep well” may be helpful to modify: (a) inappropriate sleep habits related to irregular sleep and wake times, (b) inadequate sleep environment and pre-sleep activities, and consequently (c) improve sleep parameters, such as sleep duration and sleep efficiency, and decreasing sleep latency somnolence levels.

Therefore, an experimental, prospective and quantitative study will be used to compare effects of game application by in change of habits and parameters of sleep, measured by objective and subjective tools, as well as assessing the player’s decisions as a result of playing this serious game, with the inclusion of an ecological assessment about sleep routine and bedroom organization by children. As far as our knowledge goes this is the first intervention that included a serious game to promote healthy sleep habits to children.

## Materials and Equipment

Exclusion criteria for participants will be as follows: (1) less than 7 years and more than 9 years old; (2) use of psychoactive drugs; (3) absent from interventions (in which cases data from this participant will be excluded from analysis, but they will continue to participate in the intervention) and (4) diagnose of sleep disturbance or any health problems, such as neurological disorders, and psychiatric, cardiovascular or genetic diseases. Thus, to characterize the sample and to verify inclusion criteria questionnaires and scales will be applied, and strategies developed by researchers with parents/guardians and their children. These measures and the serious game itself are described below.

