## Stepwise Procedures

### Participants

This study aims to recruit 176 healthy children enrolled in two private schools from Natal (Rio Grande do Norte – Brazil), as the number of children per class in these educational institutions ranges from 23 to 28. Schools will be selected by convenience, as there are difficulties to promote parental and school involvement (Jones et al., 2013; Wilson et al., 2014; Mindell et al., 2016), due to the concern of staff and parents about the activities developed in school and the necessity to adjust the research schedule to that of school activities, such as evaluation periods, vacation, science fair or school games. Furthermore, sample size was carried out using G^∗^Power 3.1.9, with alpha level of 5%, effect size of 0.5, and power of 95% for the two groups (Faul et al., 2007; Aberson, 2015). Results from this analysis indicated 88 participants to each group.

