### Design and Procedures

It will be used an experimental, prospective, quantitative and randomized controlled trial to compare effects of game application on change of habits and parameters of sleep, besides what the users will be able to do by playing this serious game. In order to achieve that, the following steps will be conducted: (1) randomization of participants to allocate each one in experimental or control group; (2) use of a control group that should not be submitted to intervention, to infer highest internal validity; (3) intervention with experimental group, which will allow us to evaluate if there was any modification in the parameters evaluated, determining the validity of the intervention and (4) evaluation of participants at three distinct moments throughout the study, namely: pre-intervention, immediate post-intervention and follow-up assessment, after 4 weeks (Suresh, 2011).

After selecting the schools by convenience, experimental and control groups are selected by two processes of randomization. The first will select which classes will compose the experimental and control groups in each school, throughout a basic method of randomization that is flipping a coin; in other words, one situation will be associated with each side of coin (e.g., heads – control and tails – experimental) to determinate the assignment of each class. Second, the function “Randomly assign subjects to groups” in online software GraphPad^1^ will be used to allocate participants of each class with valid data for analysis to each group.

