The control group will follow the institution’s school activities defined on the school schedule. The only moments of contact with study staff will be during evaluation, pre-, post and following intervention, to assure a proper control condition, in accordance to our research question about intervention works (Holmes et al., 2018). Considering this, further control will be needed for the following factors: contact with research team limited only to evaluation periods to avoid confusing factors such as attention, warmth, or human relationships. In the evaluation stages, the guardians will answer questionnaires and scales to assess sociodemographic and health data, sleep habits and sleep pattern of their child. The children themselves will answer: a scale to assess sleepiness levels, a questionnaire to evaluate the serious game and the game itself, will characterize their bedroom and the activities they perform before sleep. Also, teachers will be informed only essential information about the study and will be instructed to not use the knowledge acquired about sleep in class during the period of the research.

After completion of the intervention, the last two steps, post intervention evaluation and follow-up evaluation, will be conducted after 4 weeks. In these stages sleep habits and sleep patterns will be re-evaluated by the parents. Additional encounters 1 week after each evaluation will be provided to clarify any doubts about filling in the sleep diary and/or use of actiwatch. During these steps the children will be required to answer the Pictorial Sleepiness Scale of Maldonado and to characterize their bedroom and any activities that they perform before sleep at night (**Figure 2**). Thus, there will be three meetings with parents/guardians during evaluation steps, with three more other encounters to elucidate any doubt about assessments. Missing data will result in individuals being excluded without outcome.

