The second component of the serious game are four boards representing the floor of the bedroom that the children will assemble. In addition, to be more interesting and dynamic we included bonus cards (e.g., Congratulations, you do not use your cell phone before bedtime. Take out two more Perfect Bedroom Cards!) and surprise cards (e.g., You have television and computer in your room. These objects hinder the beginning of sleep! Pass the turn!). To allow the players to buy the items that will compose the bedroom bank notes with values of 1 and 2 were created. Available for the children to buy with the notes are 32 objects, divided in eight types (lamp, pillow, bed, chair, window, table, wardrobe, and fan), with four different colors (pink, yellow, green, and blue), to assemble the ‘perfect bedroom’ without electronics devices. The last pieces of the game are cards that list the objects that can be purchased and their values.

To play, all participants will receive the necessary materials described, with the starting player randomly chosen. The first participant will draw a card from the perfect room cards deck, which contains adequate (positive cards) and inadequate (negative cards) sleep habits, bonus or surprise cards. After drawing one card the player must do the card indicates. The player who wins is the one who assembles the perfect room first, with all the items on the list, or the one with the most objects in their board.

The intervention will be conducted by three previously trained researchers. It will occur at the children’s school, twice a week (on Tuesdays and Thursdays), starting at 02:00 pm, for 3 weeks in a row, resulting in six sessions of 50 min each. In each session players will be challenged to set up the “perfect bedroom.” They will apply the behavioral and environmental changes of sleep hygiene to promote healthy sleep.

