### Ethics Statement

This study was approved by the Research Ethics Committee of the Federal University of Rio Grande do Norte, Brazil (registration number 62016916.2.0000.5537). All participants (children and parents/guardians) will be volunteers and will provide written informed consent to their participation in the study. The study was conducted in conformity with the ethical standards proposed in the World Medical Association Declaration of Helsinki. In addition, the control group will receive the intervention after all evaluation stages.

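### Dropping children who miss sessions from the analysis is a post-allocation exclusion that can act only on the experimental arm, and it leaves the between-group comparison open to bias

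*Protocol article*

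**What the plan says.** In the protocol article, Materials and Equipment, item (3) of the exclusion criteria is absence from the intervention, "in which cases data from this participant will be excluded from analysis, but they will continue to participate in the intervention". The number of missed sessions that makes a child absent is not stated.

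Design and Procedures describes "use of a control group that should not be submitted to intervention", and the Ethics Statement adds that "the control group will receive the intervention after all evaluation stages". The section on the intervention gives the experimental schedule as two sessions a week for three weeks, "resulting in six sessions of 50 min each".

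Design and Procedures also contains a general rule: "Missing data will result in individuals being excluded without outcome". The same section describes allocation in two steps: a coin flip for each class, then a software step to "allocate participants of each class with valid data for analysis to each group".

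**The concern.** An eligibility criterion should be decidable before allocation. This one is not, because a child can be absent only once sessions have started. Only one arm has sessions before the outcomes are taken, so the rule keeps the more regular attenders in the experimental arm and leaves the control arm whole. The controls who would have missed sessions stay in the control mean; their counterparts leave the experimental mean.

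The article relies on randomisation and an untreated control group for internal validity, and plans t-tests and chi-square tests between the groups at each time point. Those tests keep their meaning only if the groups compared are the groups allocated. If absence goes with poorer sleep, less regular routines or less engaged parents, part of any difference would come from selection. With no threshold stated, the analysis set could also be settled after the data are seen.

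**Working it through.** **1. Which arm the rule can reach.** Experimental children have six sessions before the post-intervention and follow-up evaluations. Controls have none until all evaluations are finished. Before outcomes are measured, item (3) can therefore remove experimental children and cannot remove a control.

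**2. The plan's own sample size.** Participants gives "alpha level of 5%, effect size of 0.5, and power of 95% for the two groups" and "Results from this analysis indicated 88 participants to each group". For a t-test with d = 0.5, alpha 0.05 and power 0.95, the exact calculation gives 87.26 per group one-sided, rounded up to 88, and 104.93 two-sided, rounded up to 105. The stated 88 therefore reproduces as a one-sided calculation. Sidedness is a separate matter; it is noted here only to fix the starting point for power. The recruitment target of 176 is exactly 2 × 88, so nothing is set aside for exclusions.

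**3. How many children the rule removes.** The documents give neither an attendance rate nor a threshold, so both are assumed. If any one missed session of six counts and attendance is independent across sessions with probability p, the excluded share is 1 − p^6.

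| p (assumed) | p^6 | Share excluded | Of 88 experimental | Of 88 controls |
|---|---|---|---|---|
| 0.98 | 0.886 | 11% | 10 | 0 |
| 0.95 | 0.735 | 26% | 23 | 0 |
| 0.90 | 0.531 | 47% | 41 | 0 |

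This is the strictest reading of absence. A looser threshold, or absences concentrated in the same children, gives smaller shares.

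**4. Shift in the comparison.** Let a fraction q be excluded from the experimental arm, and let those children score g SD worse than the ones who stay. With no true effect, the whole-group mean is q × g worse than the attenders' mean, so the comparison moves by q × g SD in favour of the game. With q = 0.265 and g = 0.3 (assumed), the shift is 0.265 × 0.3 = 0.08 SD, and 0.08 / 0.5 = 16% of the planning effect. With g = 0 the shift is zero.

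**5. False-positive rate.** A simulation with no true effect, 88 allocated per arm, a two-sided 5% t-test and 6,000 runs per setting gave:

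| q (assumed) | g (assumed) | Shift (SD) | Type I error |
|---|---|---|---|
| 0.1 | 0.25 | 0.025 | 5.5% |
| 0.2 | 0.25 | 0.05 | 6.4% |
| 0.2 | 0.5 | 0.10 | 10.0% |
| 0.3 | 0.5 | 0.15 | 13.6% |
| 0.4 | 0.5 | 0.20 | 20.2% |

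**6. Power, if absence is unrelated to outcome.** On the one-sided basis that reproduces 88, power at d = 0.5 is 95.1% for 88 v 88. It is 94.2% for 79 v 88 (10% excluded), 92.9% for 70 v 88 (20%) and 91.2% for 62 v 88 (30%). The loss is about 1 to 4 percentage points.

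**The case against.** The strongest reply is that nothing in the documents shows that absentees sleep differently. Item (4) of the same list already removes children with a diagnosed sleep disturbance or health problem, which narrows one route by which absence could go with worse sleep. This stands. A reader might infer that the result is bound to be biased towards the game, but the documents support only that it is open to bias, with size and direction depending on g. The planned homogeneity tests between groups do not settle the matter, because a non-significant baseline difference does not show that selection can be ignored.

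A reader might also infer from the missing-data sentence that any child with one missing assessment is dropped. The sentence is unclear and may mean only that children lacking the outcome are left out. The between-group tests at each time point do not need all three visits, and the repeated-measures ANOVA is within groups. The rule applies to both arms, so it adds bias only if missingness is related to outcome and differs by arm. The extra meetings with parents are intended to limit such losses. That the experimental parents' workshop would change who returns diaries is conjecture.

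The exclusion shares rest on the strictest threshold and on independent attendance, so they lean high. Nor is the second allocation step clear. If the analysed groups are drawn from children who already have valid data, the counts above may not arise, although selection would remain a concern.

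None of these points removes the core: the absence rule is written in the text, takes effect after allocation and reaches one arm only.

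**Conclusion.** The concern holds in limited form. Followed as written, the absence rule replaces the allocated experimental group with its attenders and so weakens the randomised comparison. That conclusion needs no assumption, since it follows from the rule and from when controls receive the game. It is also not a detail left to an unseen analysis plan, because the article states the rule itself.

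The size is uncertain. The excluded share could be anything from negligible to the 11% to 47% worked out above, and the resulting shift is q × g SD. An illustrative 0.08 SD rests on an assumed 95% attendance per session, exclusion for any single absence, and an assumed 0.3 SD deficit in absentees. If absence is unrelated to outcome, the only cost is a modest loss of power. Confidence is high that the rule exists and acts on one arm, and low on the size and direction of any bias. The missing-data rule is a secondary matter.

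**What to change.** 1. Delete item (3) from the exclusion criteria.
2. State that children who miss sessions remain in all evaluations. The article says only that they continue in the intervention.
3. Reconcile the two allocation steps in Design and Procedures, so that each child's allocated group is fixed and does not depend on having valid data.
4. Make the primary analysis all allocated children in their allocated group, regardless of attendance.
5. Replace deletion of children with missing data by an analysis that uses every available assessment, for example a likelihood-based mixed model.
6. Report attendance, and use it only in a secondary per-protocol or dose analysis with a threshold stated in advance.

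The cost is mostly wording, plus the effort of evaluating absentees if that was not already intended. The estimate will include partially exposed children and may be slightly smaller. Recruiting more children would restore power but would not remove the selection.
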